#### 2.14.2. Emergency Unblinding

In exceptional circumstances—for example, a sequence of adverse or serious adverse events that seem to be related to the intervention—blinding will need to be broken. In such circumstances, the trial researcher will contact the chief investigator to convene an emergency trial management group meeting to review the events and consider if unblinding is necessary.

The breaking of blinding would not necessarily stop the trial but would need to be clearly reported in any publication or reports of the trial findings.

## 3. Data Collection

### 3.1. Trial Procedures and Evaluations

Participants will be asked to complete the electronic Case Record Form (eCRF) at baseline (week 0), end of treatment (week 10), and week 26 via REDCap or with the help of a trial researcher, who will enter the information into REDCap on the participants’ behalf. Table 1 shows the notification schedule for the electronic case record form process. The participants will be considered to have withdrawn from the trial if they fail to complete outcome measures within the required time frame of 14 days or do not respond to two sequential messages from their peer worker (phone or text).

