### 1.1. Objectives

The objectives of this feasibility trial address (i) the recruitment, training, and retention of peer workers, (ii) the recruitment, randomisation, and completion of intervention and outcome measures by members of the farming community with depression, and (iii) fidelity of intervention delivery. Trial feasibility will be established if the following outcomes are met:Peer workers-Ten peer workers are recruited to participate in the trial.-Eight peer workers successfully complete the Behavioural Activation training package.-Six peer workers deliver the Back-on-Track intervention to at least one participant.-Five peer workers are retained through to the completion of the trial.-Peer workers attend at least eight of the 13 group supervision sessions.Members of the farming community with depression (participants)-Approximately 200 indicated that they are interested in taking part in the research.-Forty participants meet eligibility criteria and consent to participate in the trial.-Forty participants complete baseline (week 0) measures.-Forty participants agree to be randomised.-Forty participants start the trial.-Sixteen participants complete the experimental intervention (defined as attending at least six of the 10 Behavioural Activation sessions). Note: there is no feasibility measure for level of completion for the control group given provision of treatment as usual (Managing Stress on the Farm).-Thirty-two participants complete week 10 measures.-Twenty-eight participants complete week 26 measures.Ninety percent of the Behavioural Activation sessions are delivered to an at least satisfactory level of fidelity to model (independently determined using the Behavioural Activation fidelity assessment) [20].

The trial is not powered or designed to detect statistical between-groups differences in primary or secondary outcomes, and no statistical analysis will be undertaken or reported.

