#### 2.6.2. Control (Managing Stress on the Farm)

Participants allocated to the control intervention will receive treatment as usual (primary care visits, antidepressant medication if indicated), weekly mood monitoring, and guided self-help (Managing Stress on the Farm), representing the standard first-line treatment option for people with depression. An automated email directing participants to complete their mood rating will be sent weekly along with a reminder SMS sent to their mobile phone. The workbook provides tailored information, practical activities, and links to further resources (including what to do in a crisis) to support the mental health of members of the farming community. A weekly ‘check-in’ addresses some of the attentional issues related to a self-help workbook control intervention.

An attentional control—to address the non-specific effects of the experimental intervention—was discussed as an alternative comparator intervention. Although there are methodological advantages, we did not consider an attentional control to be consistent with our ethical obligation to ensure that participants were receiving standard of care (guided self-help). That said, we acknowledge the potential that this may overestimate the acceptability of the Back-on-Track intervention.

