### 2.11. Sample Size

The intended sample size is 40 participants (approximately 20 in the intervention supported by 10 peer workers and 20 in the control groups). Sample size calculations are not appropriate for feasibility trials, and a sample of 40 is generally considered adequate to establish that a definitive trial is feasible [29].

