### 2.13. Allocation

Randomisation will be undertaken using an online randomisation service—Sealed Envelope Ltd London, UK [34]—and managed by the La Trobe University Clinical Trials Platform to ensure the research team remain blinded to group allocation. Randomisation will be by random permuted blocks with a 1:1 ratio.

The Clinical Trials Platform will contact the peer worker by phone and inform them of the allocation of a new trial participant and ask if there is any known conflict of interest with the allocated participant. If there is no conflict of interest, the peer worker will be provided with allocated participant details (name, telephone number, and email address) and will call the participant to introduce themselves and arrange the first session.

If there is a conflict of interest identified (either by the peer worker or participant), the participant will be reallocated to a different peer worker. Participants allocated to the control group will be contacted by phone by the Clinical Trials Platform to inform them of the allocation, emailed an electronic copy, and sent a hard copy of the Managing Stress on the Farm workbook in the post.

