### 3.2. Data Management

The electronic case record form will be developed by the Clinical Trials Platform. To promote data quality, the electronic case record form will be designed to minimise errors in data entry, e.g., not permitting the entry of impossible values (e.g., age of 999 years). Wherever possible, we will use drop-down menus or tick boxes that are easy for participants to accurately complete. Survey logic will be used to ensure that participants are not having to skip over or answer irrelevant questions. Participants will need to answer all compulsory questions before submission, eliminating the risk of missing data.

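### Ignoring two peer-worker messages counts as withdrawal from the trial, but only Back-on-Track participants have a peer worker, so dropout is defined differently in the two arms

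*Protocol article*

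**What the plan says.** Section 3.1 gives two alternative triggers, and either is enough. A participant is "considered to have withdrawn from the trial if they fail to complete outcome measures within the required time frame of 14 days". The same applies to those who "do not respond to two sequential messages from their peer worker (phone or text").

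Section 2.11 describes the arms as "approximately 20 in the intervention supported by 10 peer workers and 20 in the control groups". Under section 2.13, a peer worker is given the details of each participant allocated to Back-on-Track. For the other arm, "Participants allocated to the control group will be contacted by phone by the Clinical Trials Platform to inform them of the allocation", and a workbook is emailed and posted. Later contact in the control arm is automated (section 2.6.2): "An automated email directing participants to complete their mood rating will be sent weekly along with a reminder SMS sent to their mobile phone". No withdrawal rule is attached to leaving those messages unanswered.

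The abstract lists the dropout rate from the trial among the feasibility outcomes. Section 1.1 sets separate criteria for attending sessions (16 participants attend at least six of 10) and for completing measures (32 at week 10; at week 26, "Twenty-eight participants complete week 26 measures"). The two measure criteria pool the arms.

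Section 3.2 adds: "Participants will need to answer all compulsory questions before submission, eliminating the risk of missing data".

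**The concern.** Two problems lie in one sentence of section 3.1.

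- **The rule depends on the arm.** One of the two routes to being counted as withdrawn is open only to Back-on-Track participants. The reported dropout rate then reflects the definition as well as participants' behaviour. Section 2.14 already warns that knowing the allocation may affect dropout; a definitional difference added on top cannot be separated from that effect afterwards.
- **The rule merges different events.** Not answering a peer worker is disengagement from the intervention. Returning a form late is a missed visit. Neither is a decision to leave the trial. Section 1.1 keeps session attendance and measure completion apart, and section 3.1 runs them together.

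At stake are the dropout figure that a definitive trial would be planned on and, depending on what happens after such a withdrawal, the retention counts that decide feasibility.

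**Working it through.** **Step 1. Who can meet each trigger**

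| Trigger (section 3.1) | Back-on-Track | Control |
|---|---|---|
| Measures not completed within 14 days | Yes | Yes |
| No response to two sequential peer-worker messages | Yes | No, there is no peer worker (2.11, 2.13) |

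Nothing else in the article supplies a control counterpart. The weekly mood prompts (2.6.2) carry no withdrawal rule. A low or falling mood score leads to contact by a psychologist (4.4.2). The fortnightly adverse-event texts (4.2) come from REDCap, not from a peer worker. The second trigger therefore adds zero or more withdrawals in Back-on-Track and exactly zero in control, so its direction is fixed.

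**Step 2. The 14-day trigger**

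It is symmetric between arms. If the request goes out at week 10, the window closes at week 10 + 2 = 12. A participant who misses it is classed as withdrawn 26 − 12 = 14 weeks before the next assessment.

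**Step 3. Two readings of the consequence**

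Section 3.1 does not say whether measures are still requested after such a withdrawal.

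- *Not requested:* both the dropout rate and the completion counts are affected.
- *Still requested:* the completion counts are largely protected, but dropout is still defined differently by arm.

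**Step 4. Size under the first reading**

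The article derives no figure to reproduce. Its targets are 32/40 = 80% and 28/40 = 70%. Allocation is 1:1 (section 2.13: "Randomisation will be by random permuted blocks with a 1:1 ratio"), so take 20 per arm. Let *b* be base completion, set at the target rate, and *q* the share of otherwise-completing intervention participants withdrawn by the message rule. The article gives no value for *q*; 5% to 30% is an assumption.

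- Intervention completers ~ Binomial(20, *b*(1 − *q*)); control completers ~ Binomial(20, *b*).
- Artificial gap = *b* × *q*.
- The chance of meeting the target comes from the exact sum of the two counts.

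| *q* | Week 10 (*b* = 0.80): intervention v control | Gap | P(≥32) | Week 26 (*b* = 0.70): intervention v control | Gap | P(≥28) |
|---|---|---|---|---|---|---|
| 0 | 16.0 v 16.0 | 0 | 0.59 | 14.0 v 14.0 | 0 | 0.58 |
| 5% | 15.2 v 16.0 | 4 points | 0.47 | 13.3 v 14.0 | 3.5 points | 0.48 |
| 10% | 14.4 v 16.0 | 8 points | 0.35 | 12.6 v 14.0 | 7 points | 0.39 |
| 20% | 12.8 v 16.0 | 16 points | 0.17 | 11.2 v 14.0 | 14 points | 0.23 |
| 30% | 11.2 v 16.0 | 24 points | 0.06 | 9.8 v 14.0 | 21 points | 0.11 |

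With more slack the effect is milder. At *b* = 0.90 and *q* = 10%, the week 10 gap is 9 points and P(≥32) is 0.89 against 0.99.

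**Step 5. How often the message rule might fire**

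Suppose each of *n* messages is missed independently with probability *p*. The chance *f* of no two consecutive misses follows *f*(*n*) = (1 − *p*)*f*(*n* − 1) + *p*(1 − *p*)*f*(*n* − 2), with *f*(0) = *f*(1) = 1. The rule fires with probability 1 − *f*(*n*).

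- *n* = 5: 4% at *p* = 0.10 and 13% at *p* = 0.20.
- *n* = 10: 8% at *p* = 0.10 and 27% at *p* = 0.20.

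Both *n* and *p* are assumptions.

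**Step 6. Overlap between silence and non-return**

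Take four intervention participants who stop replying, and hold overall form return at 85% (34 of 40). If the four return forms at rate *r*, the other 36 return at (34 − 4*r*)/36. Compare P(≥32) with the four still asked and with them removed.

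| *r* | Rate in the other 36 | Four still asked | Four removed |
|---|---|---|---|
| 0.85 (no overlap) | 0.850 | 0.86 | 0.35 |
| 0.50 | 0.889 | 0.88 | 0.63 |
| 0.25 | 0.917 | 0.91 | 0.82 |

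The stronger the overlap, the smaller the loss.

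**The case against.** The best case for the plan is that little turns on this wording. It is a descriptive trial of 40 people with no planned between-arm test of outcomes. The asymmetry can only count against Back-on-Track retention, so it cannot by itself produce a falsely favourable feasibility result. The section 1.1 targets count people who complete measures, not people who were never classed as withdrawn. A late form follows a real chasing process: a request on day 0, reminders on days 3 and 6, and on day 8 a prompt for a researcher to telephone (Table 1), with assisted completion available.

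Much of that stands, and it rules out several stronger readings that a reader might infer:

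- *Outcome data are lost once someone is withdrawn.* The text says neither that requests stop nor that data are discarded. The probabilities in Steps 4 and 6 depend on that unstated step.
- *Both triggers bias retention by arm.* The 14-day trigger is identical in the two arms; only the message trigger differs.
- *Lopsided retention would pass unnoticed because the targets are pooled.* The arm-specific criterion of 16 participants attending at least six sessions is a partial guard.
- *A refused item turns into a withdrawn person.* Section 3.2 speaks of compulsory questions, does not say that every item is compulsory, and does not exclude an option to decline. That chain is a guess about how the form is built. In context, the missing-data remark is most naturally about items within a submitted form.

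What the objection does not answer is that dropout from the trial is itself a named feasibility outcome, and section 3.1 defines it differently in the two arms under either reading.

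**Conclusion.** The point holds as a fault in a stated rule, not as a missing detail. Followed as written, section 3.1 adds a withdrawal route in Back-on-Track that controls cannot meet, and it treats disengagement from the intervention, or one late form, as leaving the trial. The direction is certain: counted dropout can only rise in Back-on-Track relative to control.

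The size is not known from the article. If withdrawal ends follow-up requests, base completion equals the targets, and 5% to 30% of otherwise-completing intervention participants are caught, the week 10 gap is 4 to 24 points and P(≥32) falls from 0.59 to between 0.47 and 0.06. At week 26 the gap is 3.5 to 21 points and P(≥28) falls from 0.58 to between 0.48 and 0.11. These are illustrations, and they shrink where people who stop replying would not have returned forms anyway. If requests continue, the harm is mainly to the meaning of the dropout rate. The missing-data sentence in section 3.2 is a minor matter of wording.

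**What to change.** In section 3.1:

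1. Define two separate events: stopped the allocated intervention, and withdrew from follow-up.
2. Define withdrawal from follow-up identically in both arms, as withdrawal of consent to data collection.
3. Remove the two-message rule as a trigger for trial withdrawal. When sessions stop is left to the sponsor.
4. Keep requesting week 10 and week 26 measures from every randomised participant unless consent is withdrawn. Record a form later than 14 days as late or missing for that visit only.
5. Report retention by arm beside the pooled targets.

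In section 3.2, limit the missing-data claim to compulsory items within submitted forms.

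The cost is revised wording and a few more reminders and contacts with participants who have gone quiet. Sample size and the feasibility targets do not change.

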### 3.2. Data Management

The electronic case record form will be developed by the Clinical Trials Platform. To promote data quality, the electronic case record form will be designed to minimise errors in data entry, e.g., not permitting the entry of impossible values (e.g., age of 999 years). Wherever possible, we will use drop-down menus or tick boxes that are easy for participants to accurately complete. Survey logic will be used to ensure that participants are not having to skip over or answer irrelevant questions. Participants will need to answer all compulsory questions before submission, eliminating the risk of missing data.

### 3.3. Statistical Methods

Descriptive statistics (predominantly number and proportion) will be used to summarise the feasibility outcomes from our trial. We will report means and standard deviations for the five outcome measures at the three trial time-points but will not undertake any statistical analysis.

## 4. Economic Evaluation

The economic evaluation reporting will adhere to the Consolidated Health Economic Evaluation Reporting Standards (CHEERS) statement [35]. A cost-consequence analysis will explore the costs associated with the programme and report these alongside potential benefits and outcomes. A cost-consequence analysis (CCA) is a form of economic evaluation where costs and outcomes are listed separately rather than combined into a single metric (such as a cost-effectiveness ratio). This approach allows decision-makers to consider a range of impacts and make context-specific judgements about value and trade-offs. The analysis will be conducted from the ‘funder perspective’, allowing health care organisations to consider implementation cost for this and similar programmes.

Consequences will include the primary clinical outcome of depressive symptoms (measured by change in PHQ-9), along with secondary outcomes such as enhanced work performance (Work Productivity and Activity Impairment questionnaire), reduced loneliness (UCLA Loneliness Scale), improved wellbeing (WHO-5), and health-related quality of life (AQoL-4D). Patterns of health service use (e.g., GP visits, hospital presentations, mental health service contacts) will also be reported as a key outcome, reflecting potential shifts in demand associated with the intervention. These outcomes capture a broad range of potential programme benefits and align with the lived experience goals of the target population.

Costs and outcomes will not be aggregated into a single cost-effectiveness ratio, in line with the cost-consequence approach, but will be presented in a disaggregated format to support decision making. Sensitivity analyses will be conducted to test assumptions around intervention delivery costs and variability in health service use. In addition, outcomes such as the AQoL-4D will provide utility weights that may be used in future cost-utility analyses.

Findings from this feasibility-phase CCA will directly inform the design of a future definitive trial, including refinement of data collection tools, choice of primary outcome, and economic parameters. The results will also be used to support the development of a longer-term economic model (e.g., decision tree or Markov model) to estimate cost-effectiveness over time. This model will enable estimation of cost-per-quality-adjusted life years (QALY) gained and provide critical information for funders and policymakers considering broader implementation.

### 4.1. Process Evaluation

#### 4.1.1. Interviews with Peer Workers and Trial Participants

Peer workers interviews will be conducted at the end of the trial once all Back-on-Track sessions are complete. Interviews will assess the acceptability, feasibility, barriers, and facilitators to delivering the Back-on-Track intervention.

Interviews with 10 participants (five from each group) will be conducted to assess the acceptability, feasibility, barriers, and facilitators to engagement with the trial. All interviews will be conducted as soon as possible after intervention group participants have completed their final Back-on-Track session and after control group participants have completed week 10 assessment measures.

Interviews will be conducted by research team members following a semi-structured interview schedule and transcribed using a transcription service. We will use the framework method, following [36], to analyse the interviews.

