### 2.14. Blinding (Masking)

This is a single-blind trial. All research team members will be masked to group allocation with the exception of the Clinical Trials Platform team, who will need visibility of allocation to provide contact details to peer workers and mail resources to participants in the control group. Peer workers will be delivering the intervention and as such will not be masked.

As part of the consent process, a full explanation of the trial design will be given to participants including a description of the Back-on-Track (experimental) and Managing Stress on the Farm self-help workbook (control) interventions. Consequently, participants will not be blind to group allocation (an open-label trial). Awareness of group allocation can impact how participants respond to the intervention they receive. Participants who know they have been allocated to Back-on-Track may have more favourable expectations than those allocated to the Managing Stress on the Farm group, who may feel disappointed. Participants in the trial may assume that Back-on-Track will be better than Managing Stress on the Farm. Telling participants which intervention they will receive may also influence how participants complete outcome assessments. It is also possible that knowledge of treatment allocation may also impact participant compliance and dropout from the study. It will be important when interpreting the outcomes of this feasibility trial to acknowledge the context within which the research was conducted.

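### Control interviews wait for the week 10 measures but Back-on-Track interviews do not, so up to five Back-on-Track participants, and no controls, could be interviewed before giving week 10 outcomes

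*Protocol article*

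**What the plan says.** Section 4.1.1 of the protocol article gives the number of interviews as "Interviews with 10 participants (five from each group"; their purpose is "to assess the acceptability, feasibility, barriers, and facilitators to engagement with the trial". Members of the research team conduct them, using a semi-structured schedule.

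The timing rule has one part for each arm. Interviews are to be held as soon as possible after "intervention group participants have completed their final Back-on-Track session and after control group participants have completed week 10 assessment measures".

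Section 3.1 places the second assessment at week 10, labels it the end of treatment, and expects the outcome form "within the required time frame of 14 days". Table 1 sends the request on day 0 and reminders on days 3 and 6, and alerts a researcher on day 8 to telephone anyone who has not responded.

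Section 2.14 states that participants know their allocation and accepts that "Telling participants which intervention they will receive may also influence how participants complete outcome assessments". Sections 1.1, 2.7 and 3.3 limit the use of the outcome measures to description, with no efficacy analysis. One feasibility criterion in Section 1.1 is that 32 participants complete the week 10 measures.

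**The concern.** The rule fixes the order of outcome form and interview in one arm only. A control always answers the week 10 questionnaires first. A Back-on-Track participant may first have a conversation with the research team about how acceptable the trial was and what helped or hindered engagement, and then complete the PHQ-9, the UCLA loneliness scale, the WHO-5, the work productivity questionnaire and the AQoL-4D.

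Two things could follow. Reflecting on the intervention just before completing self-report measures could colour the answers of participants who already know their arm. A personal contact while the form is open could also prompt some of them to return it. Either would act in one arm only and come from the interview schedule, not from the intervention. The week 10 means, the week 10 completion count and the outcomes listed in the cost-consequence analysis (Section 4) are the figures exposed. The same timing might also be carried into the definitive trial, where change in PHQ-9 is the proposed primary outcome.

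**Working it through.** The plan states no figure on this point, so there is none to reproduce. The check is whether the written rules allow the interview to come first, and for how many participants.

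**Step 1: the order allowed in each arm**

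| | Back-on-Track | Control |
|---|---|---|
| Interview trigger (4.1.1) | final session completed | week 10 measures completed |
| Week 10 form (3.1) | up to 14 days to complete | up to 14 days to complete |
| Interview before form? | possible | excluded by the rule |

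No other section makes Back-on-Track interviews wait for the form.

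**Step 2: how many**

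- Interviewed per arm: 5 (4.1.1). Planned arm size: about 20 (2.11).
- Back-on-Track ceiling: 5/20 = 25% of the arm. Floor: 0/20 = 0%, if every interview happens to follow the form.
- If the arm returns 16 forms (80%, the rate implied by 32 of 40) and all five interviewees are among them, the ceiling is 5/16 = 31% of returns.
- Controls: 0 by construction.

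**Step 3: can the timing be narrowed further?**

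The article gives ten sessions (2.6.1) but no interval between them, no time from baseline to the first session, and no interview lag beyond as soon as possible. All three have to be assumed. Take weekly sessions, so that the last falls 9 × 7 = 63 days after the first.

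- Final session: day 63 + start delay
- Interview: final session + lag, with the lag uniform on 0 to 7 days
- Form returned: day 70 + delay, with the delay uniform on 0 to 8 or on 0 to 14 days

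The simulated probability that the interview precedes the form, with the start delay uniform over the range shown, is:

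| First session, days after baseline | Form delay 0–8 days | Form delay 0–14 days |
|---|---|---|
| 0–7 | 85% | 92% |
| 0–14 | 54% | 71% |
| 0–21 | 36% | 50% |
| 0–28 | 27% | 37% |
| 7–21 | 11% | 29% |
| 14–28 | 0% | 4% |

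With the first session at 7 to 21 days and an interview lag of 0 to 14 days, the figures are 5% and 17%.

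Multiplying by five interviewees, the expected number interviewed first runs from 5 × 0.00 = 0 to 5 × 0.92 = 4.6. The results cover almost the whole of the 0 to 5 range, so the documents support the bounds and nothing narrower. The model also leaves out two cases: a participant who stops sessions early could be interviewed well before week 10, and one whose sessions run past the form window would be interviewed after it.

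**The case against.** The different anchors have an ordinary explanation. Controls have no final session, so week 10 is their natural marker, and the article treats week 10 and end of treatment as one time-point. Nothing in Section 4.1.1 says that interviews should come first. This explains how the wording arose, but it does not close the gap: the article states a rule for each arm, and only the control rule protects the order. Reading the sentence jointly, so that every interview waits for both events, does not help either, because the form it names is the controls' form.

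A reader might infer that five Back-on-Track participants will be interviewed first, or that most will. The documents do not support that. Five is a ceiling. Section 2.13 puts several steps between randomisation and the first session: a call to the peer worker, a conflict-of-interest check, possible reassignment, and a call to arrange the session. A start on or near day 0 is therefore optimistic, and a delay of two to four weeks makes the problem nearly disappear under weekly sessions.

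A reader might also multiply an assumed change in PHQ-9 by the share interviewed and quote a shift in the arm mean. No section supports any size or direction of change, and the interview concerns engagement with the trial, not symptoms. No such figure should be quoted.

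Finally, no efficacy conclusion rests on these data, no feasibility criterion uses a PHQ-9 value, and the cost-consequence analysis forms no ratio. The week 10 completion criterion is pooled over both arms. At 80% return, about 5 × 0.20 = 1 of five interviewees would otherwise not return the form, and everyone already receives the Table 1 prompts. These points stand and keep the matter minor. They do not justify leaving an avoidable difference between arms in place.

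**Conclusion.** The point holds as a minor one. Section 4.1.1 lets between 0 and 5 of about 20 Back-on-Track participants (0% to 25%), and no controls, be interviewed about the trial before they give their self-reported week 10 outcomes. The bounds rest only on the stated interview numbers, the planned arm size and the two triggers. Where in that range the trial will fall depends on session spacing, start delay and interview lag, which the article does not give.

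The size of any effect on PHQ-9 answers or on form completion is unknown. Because outcomes are reported descriptively and the completion criterion is pooled, the consequence is small. It would go too far to say that the week 10 means will be biased or that the 32 of 40 criterion is at risk; neither follows from the documents. The case for acting is that the difference is avoidable, sits in one arm, and is cheap to remove in a trial whose purpose is to test procedures.

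**What to change.** Replace the timing sentence in Section 4.1.1 with one trigger for both arms: *Interviews take place after the participant's week 10 measures have been submitted or the 14-day window has closed and, for Back-on-Track, after the final session.*

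The clause on the closed window keeps a participant who misses the form from being barred from interview by that alone. As Section 3.1 treats such a participant as withdrawn, the team should confirm whether an interview may still be offered.

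The cost is one sentence. Some Back-on-Track interviews would take place days to about two weeks later, with slightly longer recall of the sessions. Treatment, sample size and analysis do not change.
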